## Abstract

**Background:**

Impaired gait adaptability is one of the major causes of falls among older adults owing to inappropriate gait adjustments in cluttered environments. Training programs designed to improve gait adaptability behavior in a systemic approach may prevent falls in older adults. Recently, virtual reality (VR) technology has been prominent as a relevant gait training tool because of its training implementation potential.

**Objective:**

This study was designed to compare the effectiveness of a VR-based gait training program (VR group) for improving gait adaptability behavior and, thus, reducing the risk of falls relative to a conventional training program such as Nordic walking (NW; NW group). We hypothesized that the VR-based gait training program will lead to greater gait adaptability improvements.

**Methods:**

We will be conducting a randomized controlled trial with pretests, posttests, retention tests, and follow-up. In total, 40 healthy independent-living community dwellers (aged between 65 and 80 years) will be allocated, after a general medical examination, to the VR or the NW group for a training program of 6 weeks. Primary outcomes related to gait adaptability capacities (ie, analysis of adjustments made in different locomotor tasks) and acceptance of the VR device (ie, analysis of acceptance) will be assessed before and after the intervention and 1 month after the completion of the training program (retention). A follow-up will be done during the 12 months after the completion of the gait training program.

**Results:**

Data collection will begin in September 2025, and the first results are expected in December 2025.

**Conclusions:**

The findings of this study may demonstrate the relative relevance of a gait training program in VR versus a conventional one for improving gait adaptability behavior in healthy older adults and, thus, prevent the chances of a fall.

**International Registered Report Identifier (IRRID):**

PRR1-10.2196/57866

## Introduction

### Fall Prevention in Older Adults

Falls are a significant health issue because they lead to severe injuries, hospitalizations, and death [1,2]. They also lead to serious physical and psychological restrictions after the fall, with a decline in social activities and a reduced quality of life [3]. Repeated falls often occur after a first fall [4]. Given that fall history is the strongest predictor of future falls [5], gait training programs must also be offered to healthy older adults with no fall history. Therefore, these fall prevention programs must be developed to avoid (or at least delay) the first fall occurrence leading to potential, future repeated falls.

Impaired gait adaptability, which is the ability to adjust locomotion parameters to move safely in cluttered environments, is one of the major causes of falls among older adults [6,7]. In cluttered environments, inappropriate gait adjustments can cause older people to hit obstacles or distribute stride length adjustments less than optimally and thus cause falls [2,8,9]. Some studies have shown that impaired gait adaptability is associated with a high risk of falls in older adults [10-12]. To prevent falls in older adults, training programs, including physical activity, designed to improve gait adaptability are thus particularly relevant [13,14].

In fall prevention, several studies have shown the beneficial effects of physical activity, focusing either on one specific (analytic approach) or multiple (systemic approach) physical components [15-18]. In this study, we decided to focus on training programs with a systemic approach, which have been shown to lead to greater improvement of both functional capability and quality of life compared with those based on an analytic approach [19,20].

### Gait Training Programs Adopting a Systemic Approach to Prevent Falls

Training programs adopting a systemic approach can be provided by conventional gait training (without the use of dedicated technologies) or by gait training using new technologies.

#### Conventional Gait Training

In conventional gait training, Nordic walking (NW), defined as “Scandinavian walking with poles,” appears, for instance, as a relevant physical activity in the fall prevention context. This type of walking training promotes an easily accessible physical activity that can be performed by many people to improve their gait capacities [21]. Recent systematic reviews showed that NW training leads to beneficial effects on many biomechanical parameters and motor skills development [22] and appears as a promising and effective way to improve motor capacities in older adults [23], such as increases in arm-leg coordination [24], gait speed and step length [25], and postural control and gait parameters [26-28]. Gait improvements obtained by NW training also reduce the risk of falls [29]. However, in recent years, the use of new technologies has given new impetus to the development of gait training programs based on a systemic approach [30].

#### Extended Reality at the Service of Gait Training

Among these new technologies, extended reality (XR) is an emerging technology that involves virtual reality (VR), augmented reality (AR), and mixed reality [31]. VR is defined as a computer-simulated environment that includes real-time simulation and interaction through multiple sensory channels and a sense of being physically and psychologically present in another place by completely occluding the real world [31]. Contrary to VR, the real world is not occluded in AR: virtual objects are overlaid in the real-world environment. In the same way as in AR, in mixed reality, virtual objects are overlaid in the real-world environment; however, users can physically interact with these virtual objects.

Several studies have demonstrated the effectiveness of XR gait training on balance and gait ability in older adults [32-37]. Shema et al [36] conducted a 5-week VR gait training program for older adults with a fall history. Participants walked on a treadmill and performed obstacle negotiations during a virtual course, while their displacement was displayed in a virtual environment (VE) represented on a screen located in front of them. In their study, Mirelman et al [35] provided a 6-week VR gait training program for older adults with a high risk of falls. During the training sessions, participants walked on a treadmill and performed several goal-directed locomotion tasks (ie, multiple obstacles and paths either with or without distractors), while their displacement was displayed in a VE represented on a screen located in front of them. For their part, van Ooijen et al [37] provided a 6-week AR gait training program for older adults with fall-related hip fractures. Participants walked on an instrumented treadmill on which a visual context was directly displayed on the belt, proposing various goal-directed locomotion tasks (eg, stepping and obstacle avoidance).

These XR gait training programs led to greater improvements in gait ability and thus a reduction in the risk of falls compared with conventional ones [35-37]. However, the implementation of these programs may have some limitations in terms of gait training relevance. Consequently, some precautions need to be considered to identify areas for improvement of XR gait training programs.

#### Four Precautions for XR Gait Training Program Implementation

##### Precaution 1: Preserving the Ecological Validity of the XR Setup

The actual use of these XR devices may be examined to ensure the ecological validity during gait adaptability training programs [38] in terms of the level of immersion and locomotion.

First, the level of immersion is an important characteristic of XR devices in training implementation [39] because a high level of immersion leads to high engagement and enjoyment [40]. The XR setups used in previous studies did not make it possible to provide a high level of immersion. Shema et al [36] and Mirelman et al [35] used the same VR setup, which provided a third-person view of the foot avatar in the VE presented on a small screen in front of the participants, leading to a low level of immersion. An immersive experience with a first-person view (ie, the transposition of the usual user’s viewpoint into the VE) seems primordial in a gait training program intended to improve gait adaptability capacities. In their review, Liu et al [38] demonstrated that the use of fully immersive XR devices with older adults induced greater gait improvements compared with nonimmersive ones. Future XR gait training program implementation with older adults should be based on the use of a fully immersive XR device (as a VR head-mounted display [VR-HMD]).

Second, in the 3 previous studies, older adults walked on a treadmill. This constitutes a second limitation in gait training implementation, given that the use of a treadmill gives rise to partly different gait kinematics compared with natural locomotion (eg, sagittal plane kinematic differences at foot strike [41]). Conversely, overground locomotion preserves natural locomotion, allowing a high level of ecological validity and natural interaction with virtual objects [42,43].

A recent study underlined the high ecological validity of a VR setup that combines a fully immersive experience and overground locomotion. Delbes et al [44] aimed to compare the gait behavior of older adults during a similar goal-directed locomotion task (ie, a simple locomotor pointing task) performed in the real world and in VR. In the 2 conditions, participants walked and performed the task with overground locomotion. In the VR condition, participants wore a VR-HMD displaying 2 VEs: a replica of the real one and a new environment. The authors demonstrated the similarity of the gait adaptability behavior produced in the real world and in VR. The use of a VR-HMD coupled with overground locomotion appears particularly relevant for future XR gait training program implementation by (1) ensuring a first-person view with a high level of immersion, (2) ensuring nonconstraint locomotion, and (3) proposing enjoyable scenarios that mimic real-life tasks.

##### Precaution 2: Following Motor Learning Principles

According to Hendry et al [45], gait adaptability training program implementation should be based on 4 motor learning principles.

The first principle is related to the variability of practice, which is necessary to optimize the improvement of gait adaptability behavior in older adults. Task variability is crucial for learning optimization by confronting older adults with a large range of potential gait adjustments based on their own gait capacities. In previous studies, older adults were confronted with various environmental lighting conditions [36]; changes in the number, size, and shape of obstacles [35]; and configurations of obstacles [37] with a training progression. Future XR gait training implementation should include the manipulation of variability based, for example, on the modulation of VE spatial constraints (obstacle characteristics and configurations).

The second principle is related to the amount of practice and, more precisely, to task repetitions. Performing any repetitions is a *sine qua non* for optimizing any learning [45]. In previous studies, experimenters provide a very global estimation of the amount of practice, for example, 15 sessions of 60 minutes [36], 18 sessions of 45 minutes [35], and 30 sessions of 40 minutes [37]. However, there is no precise information about the number of repetitions for each task performed. The combination of these first 2 principles underlines the importance of the concept of “repetition without repetition” [46,47]. Future XR gait training implementation should be based on a large amount of practice (task repetition) coupled with a large variability of practice.

The third principle is related to the individualization of the training content based on individual characteristics (eg, foot size and leg length) to lead to greater effects of the gait training program [20,48]. In previous studies, task manipulation cannot be regarded as task individualization of the training content because task configurations were manipulated without considering individual characteristics. Mirelman et al [35] manipulated the treadmill speed and the duration of training. However, this kind of task configuration was only based on the modulation of global parameters. Task individualization should also provide a gradual increase in task difficulty based on individual capacities and performance to induce an appropriate level of challenge to optimize motor learning and engagement [45,48]. In summary, future XR gait training implementation should include individualized training content based both on considering the anthropometric characteristics of the participants and on their rate of progress.

The fourth principle is feedback supplementation during the training sessions, which improves motivation, engagement, and adherence and enhances motor learning [45,49]. Various types of visual and auditory feedback, informing about performance and results, were provided during training sessions in previous studies [35-37] and at the end of the sessions in the study by Mirelman et al [35]. Future gait training program implementation should provide feedback (ie, knowledge of performance and result) with a gradual decrease in the frequency of feedback over the training program. Finally, to optimize motor learning, feedback may be requested by the participant to avoid a guidance effect [50].

##### Precaution 3: Choosing the Right Level of Analysis to Characterize the Effect of Training

In previous studies [35-37], the examination of gait behavior was limited to gait parameters reflecting only the participant behavior (eg, gait speed, step width, step length, and cadence). As mentioned previously, an analytic approach (based on the measure of global gait behavior parameters) only allows an overall understanding of the gait behavior of older adults. However, a precise characterization of participant behavior in relation to the environment (ie, the state of the agent environment system) is needed to provide a better understanding of the improvements induced by gait training.

Additional levels of analysis are consequently required to study gait adaptability behavior appropriately during goal-directed locomotion tasks. During obstacle negotiation, the evolution of the state of the agent environment system can be investigated through intertrial and trial-by-trial analyses, which allow gait adjustment strategies to be characterized in relation to obstacles (eg, the modulation of each footfall target distance [and its variability] over the obstacle approach). Gait adjustments are indeed based on a continuous coupling between information and movement [51]. These additional levels of analysis allow us to investigate the agent environment system as a whole and not the agent alone. Finally, the study of global gait behavior (as done in previous studies) coupled with the study of gait adaptability behavior (ie, based on gait adjustment indicators of the state of the agent environment system) constitutes complementary levels of analysis to characterize gait behavior in older adults more precisely.

##### Precaution 4: Studying the Acceptance of the XR Device Used

Merely examining the effectiveness of a training program is not sufficient. Acceptance of the XR device should also be investigated because attitudes of older adults toward the technology used in the training program may influence its effectiveness [52,53]. The fact that the use of an XR device is objectively effective does not mean that it is necessarily accepted, and, conversely, an XR device that is accepted is not necessarily effective. However, in the studies by Mirelman et al [35], Shema et al [36], and van Ooijen et al [37], only the effectiveness of XR gait training programs was proven without considering the acceptance of the XR device by older adults.

Some studies have investigated the acceptance of XR devices in older adults, for instance, acceptance before the first use of a VR-HMD intended to prevent falls [53]. This study revealed that older adults’ intention to use the VR-HMD was positively predicted by perceived usefulness, perceived ease of use, and perceived enjoyment and that no initial blockages appeared among older adults before the first use. Moreover, Delbes et al [44] compared acceptance before and after the use of a VR-HMD specifically intended to prevent falls among older adults. They highlighted that older adults did not intend to use the VR-HMD before the first use, but they did not refuse it either (ie, neutral attitudes toward VR-HMD before the first exposure). Finally, they intended to use it after the first effective use during a single session in VR.

To date, no study has shown the potential evolution of acceptance of the VR-HMD by older adults throughout a gait training program intended to prevent falls. As the study of the effectiveness of an XR gait training program cannot be done without ensuring that the XR device is accepted [52], the effectiveness of the program and the acceptance of the device will be conjointly investigated, in contrast to previous studies.

### Objectives of the Study and Hypotheses

The ambition of our study is to investigate both the effectiveness of a VR gait training program (using a VR-HMD) and the acceptance of the VR device among healthy older adults. The effectiveness of the VR gait training program will be compared with that of a conventional training program of NW. The choice to compare a VR gait training program method to NW reflects the ambition of this work. From our point of view, NW offers the ecological context that is most conducive to the maintenance and even improvement of the functional relationships between perception and action. The walker must constantly adjust locomotion parameters in reference to obstacles to produce adaptive behavior in cluttered environments. Our VR gait training program aims to be the counterpart of NW in a perfectly controlled context thanks to VR technologies. Demonstrating the potential of our protocol would seem more convincing to us if it were established that the improvements induced by using a VR device were equivalent or even superior to those induced *via* NW. The comparison of the gait training programs’ effectiveness will be based on a pre- and postintervention comparison of gait adaptability capacity improvements based on further levels of analyses (as presented earlier). The 2 gait training programs will be offered to healthy older adults (with no fall history) with a systemic approach to fall prevention intended to avoid or at least delay the first fall occurrence. The study of VR-HMD acceptance will be based on the Technology Acceptance Model (TAM) [54-56].

The VR gait training program will be implemented following the different guidelines presented earlier. On the basis of all the previous precautions, our future gait training program in fully immersive VR may potentially improve both functional and psychological outcomes. We hypothesize that both gait training programs will lead to improvements in gait adaptability behavior capacities (hypothesis 1) but that the VR gait training program will induce greater improvements in gait adaptability capacities in comparison with the NW training (hypothesis 2). Finally, we hypothesize that older adults will accept the VR-HMD before the VR gait training program (hypothesis 3) but that acceptance will increase throughout the gait training program (hypothesis 4).

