### Study Design

This study is based on a comparison of a gait training program in VR (ie, the VR group) with sessions of NW (ie, the NW group). Participants who meet the inclusion criteria will be randomly allocated to the gait training program (in the VR or NW group) using a computer-generated block randomization with a block size of 30 participants (1:1 rate). The data for participants in both groups will be obtained at 3 different times: 1 week before the beginning of the training program (T0), 1 week after completion of the training program (T1), and 1 month after completion of the training program (retention assessments; T2). Moreover, a follow-up (T3) with the incidence of trips and falls will be done during the 12 months after completion of the gait training program. Participants’ flow is presented in Figure 1.

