### Gait Training Programs: NW Versus VR

#### Overview

The 2 gait training programs will be dose-matched in terms of duration (ie, 45 min per session) and frequency (ie, 3 sessions per week) of training over a 6-week program (ie, 18 training sessions) following the methodology used in previous gait training studies [35-37]. Previous studies have shown that extensive practice is important for the consolidation and retention of motor memory [68]. Therefore, in line with our ambition to develop long-term improvements in gait adaptability behavior, a large amount of practice in our gait training programs is necessary.

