#### Gait Adaptability Test

Gait adaptability capacities will be assessed by a specific gait test created to assess gait parameters during goal-directed tasks. Feet positions will be measured by a 7-m-long portable pressure-sensitive walkway, GaitRite (CIR Systems, Inc), in the real world. The security system (safety harness connected to an in-ceiling rail by a lanyard) will also be used to carry out the tests. First, participants will be instructed to walk at a normal pace on the walkway. The average preferred gait speed, step length, and step duration (with their variabilities) will be calculated over 6 trials. Afterward, physical obstacles will be placed on the walkway. Participants will perform 3 different locomotor tasks: simple locomotor pointing, crossing-over, and stepping-over tasks (Figure 3). They will perform 10 trials of each goal-directed task. Participants will be instructed to negotiate obstacles as quickly as possible without colliding with them. The size of the obstacles will be proportional to the anthropometric data of the participants (ie, based on individual leg length).

For the locomotor pointing task, participants will be instructed to place the right foot tip as close as possible to the lower extremity of the target. The pointing performance (ie, the horizontal distance between the tip and the lower extremity of the target) will be measured. For the crossing-over task, participants will be instructed to cross an obstacle with a depth of 60% of their leg length. The crossing performance (ie, the horizontal distance between the tip and the lower and upper extremities of the target) will be measured. For the stepping-over task, participants will be instructed to step over an obstacle with a height of 20% of their leg length. The stepping performance (ie, the vertical distance between the tip and the target) will be measured using Kinovea Video analysis software (version 0.8.15; 2006-2011 Joan Charmant and Contrib). The position of obstacles will be manipulated (3 different positions each separated by 30 cm intervals) and presented in a randomized order (2 trials for each position condition) to avoid locomotor regularities and prevent any calibration of the distance being covered. Finally, participants will perform 10 trials of a mixed condition: a combination of 2 previous goal-directed tasks (Figure 3).

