By recording successive feet positions in relation to the obstacles, gait adaptability behavior will be analyzed through intertrials and trial-by-trial analyses [44,51,72].

In the intertrial analyses, the SD of the toe-obstacle distances and the SD of the step lengths will be measured. If the locomotion behavior produced is functional, the intertrial analysis should reveal inverted patterns of variability [44,51]. This result reveals that step length adjustments are produced to minimize toe-obstacle distance at the last footfall and thus perform optimal foot positioning. We hypothesize that the training carried out should accentuate the presence of compensatory variability (pre- vs posttest comparison) but also that the compensatory variability produced following the training should be more pronounced for the VR group than for the NW group.

The trial-by-trial analysis makes it possible to identify precisely for each trial the presence of adjustments of the step lengths and their distribution throughout the trial by comparing each step length with the average pattern of step length (see the study by Montagne et al [72] for a similar procedure). The second part of the analysis consists in computing for each step the number of adjustments needed to place the foot on the target and the number of adjustments actually implemented [44,72]. Here again, we hypothesized that the training carried out should enable participants to improve their ability to produce adaptive behavior. More precisely, not only should step length adjustments be initiated sooner after training (ie, after the test) so that they can be spread over a larger number of steps but also the adjustments produced should more accurately reflect the adjustments required to succeed in the task. These improvements in adaptive locomotor skills should be more pronounced for the VR group.

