### Differences in Effectiveness on Secondary Variables

In terms of functional capacities and psychological variables, both gait training programs should lead to improvements. Physical activity adopting a systemic approach provides beneficial effects on physical and psychological components, which are linked to gait behavior and thus to fall prevention [20,64]. However, due to VR’s large potentiality in gait training program implementation, improvements after the VR training (and long-term effects) should be greater on these general health components.

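### Hypothesis 1 credits pre-to-post gains in each arm to training, but both arms are trained and there is one pretest, so a shared gain cannot be separated from retesting, expectation or time

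*Protocol article*

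**What the plan says.** Hypothesis 1, in Objectives of the Study and Hypotheses, reads "We hypothesize that both gait training programs will lead to improvements in gait adaptability behavior capacities (hypothesis 1"). The same section bases the evaluation of effectiveness on a "pre- and postintervention comparison of gait adaptability capacity improvements".

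The Gait Adaptability Test section makes the attribution explicit for the intertrial analysis: "the training carried out should accentuate the presence of compensatory variability (pre- vs posttest comparison"). It says much the same of the trial-by-trial measures. Differences in Effectiveness on Secondary Variables extends the expectation: "In terms of functional capacities and psychological variables, both gait training programs should lead to improvements".

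On design, Study Design says: "This study is based on a comparison of a gait training program in VR (ie, the VR group) with sessions of NW (ie, the NW" arm). The first two assessments are "1 week before the beginning of the training program (T0), 1 week after completion of the training program (T1"), and a retention assessment (T2) follows one month after training ends. Training runs "over a 6-week program (ie, 18 training sessions"). Table 1 schedules the same gait test at T0, T1 and T2. Of the three single obstacle tasks, the test section says "They will perform 10 trials of each goal-directed task", and ten mixed trials follow. Statistical Analysis plans within- and between-group comparisons by repeated measures ANOVA with Tukey post hoc tests.

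**The concern.** Hypothesis 1 is about what each programme does, and the evidence for it is change within each arm. Change within a trained arm is the sum of any training effect and everything else that differs between the two visits. That includes a second exposure to a purpose-built obstacle test, the expectation of having improved, and other effects of time. To isolate the training part, a design needs an untrained group or a repeated baseline. This one has neither.

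Randomisation does not help here. It makes the arms comparable with each other, so a shared retest gain cancels in VR versus Nordic walking. It does not make T0 comparable with T1 within an arm.

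What is at stake is one of four numbered hypotheses and the parallel expectation for the secondary variables. If both arms improve, hypothesis 1 as worded would be read as confirmed, although the same data could arise with no training effect in either arm.

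**Working it through.** **What identifies each hypothesis.** Write the expected T0-to-T1 change as r + a in the VR arm and r + b in the Nordic walking arm. Here r is the shared retest, expectation and time component, and a and b are the training effects.

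- Hypothesis 2 uses (r + a) − (r + b) = a − b. The shared component drops out.
- Hypothesis 1 asks whether a > 0 and b > 0. The data give only r + a and r + b. With no untrained arm and no second pretest, r cannot be estimated, so a and b cannot be separated from it.

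**Why r need not be zero.** From the timing in Study Design and Overview, T0 to T1 spans about 1 + 6 + 1 = 8 weeks. Each visit includes 3 × 10 + 10 = 40 obstacle trials. Obstacle positions are randomised so that participants cannot calibrate the distance. That acts on distance calibration, not on general familiarity with the tasks carried from one visit to the next. The mixed-condition score is multiplied by walking speed, so greater ease with the test could raise it.

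**The plan's own figure.** Sample Size gives f = 0.2, α = .05, power .80 and 50 participants. The number of measurements m and the correlation ρ are not stated. For a repeated measures ANOVA with two groups, λ = f²·N·m/(1 − ρ). With m = 2 and ρ = 0.5 assumed:

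- N = 50: λ = 0.04 × 50 × 2/0.5 = 8.0, power 0.791.
- N = 52: λ = 8.32, power 0.807.

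The stated 50 is therefore reproduced to within two participants under those assumptions. With two groups and two time points, the time effect and the interaction have the same degrees of freedom and the same λ. A design powered for hypothesis 2 at f = 0.2 is equally sensitive to a shared time effect of that size.

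**Illustration of size.** Assume a = b = 0, and let r be d standard deviations of the change score. For the pooled time effect over N completers, the test statistic is noncentral t with N − 2 degrees of freedom and noncentrality d·√N. With N = 50 the two-sided 5% critical value is 2.011.

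| d (assumed) | d·√50 | P(time effect significant) |
|---|---|---|
| 0 | 0 | 0.05 |
| 0.2 | 1.41 | 0.28 |
| 0.3 | 2.12 | 0.55 |
| 0.4 | 2.83 | 0.79 |
| 0.5 | 3.54 | 0.93 |

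The interaction test (hypothesis 2) stays at 0.05 in every row. For d = 0.3 to 0.5 the range is 0.46 to 0.87 with 40 completers and 0.63 to 0.97 with 60, so a larger trial makes the misreading more likely.

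**Dependence on the test used.** If hypothesis 1 is instead judged by requiring significance in each arm separately, with 25 per arm, an unadjusted paired test is significant in one given arm with probability 0.302 at d = 0.3 and 0.67 at d = 0.5. It is significant in both arms with probability 0.302² = 0.09 and 0.67² = 0.45. With Tukey adjustment over the four group-by-time cells (pooled error, critical value 3.76/√2 = 2.66), the both-arms probabilities are about 0.02 and 0.21.

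**The case against.** **The active comparator is a deliberate, argued choice, and the main conclusion does not rest on hypothesis 1.** This stands. The objective, the stated aim in the Discussion and the Conclusions all concern VR against Nordic walking. A reader might infer that the missing untrained arm undermines the trial's main result. It does not, because a shared retest gain cancels in that contrast. The point is confined to hypothesis 1 and the other within-arm statements.

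**Hypothesis 1 is an expectation, and no text commits the authors to reporting that both programmes work.** That is fair as far as it goes. But it is a numbered hypothesis in causal terms, the test section attributes the pre-post change to training, and within-group comparisons are planned. The limitations section offers no caution.

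**Participants may be familiarised with the test before T0.** A reader might infer from the test description that T0 is the first contact with the tasks. The document does not establish this: the article is silent, and a condensed report may leave practice trials to the full protocol. No criticism is made on that ground. Familiarisation would reduce retest learning, but it would not remove expectation or time effects, so the main point does not depend on it.

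**The percentages depend on an assumed gain and on the choice of test.** This also stands. With Tukey-adjusted tests required in both arms, the probability falls to about 2% to 21%. The figures show how the inference could fail; they do not estimate how often it will.

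**Conclusion.** The point holds for hypothesis 1, the pre-post statements in the Gait Adaptability Test section and the secondary expectation that both programmes will improve function and psychological state. In each, a within-arm T0-to-T1 gain is credited to training, and the stated design (two trained arms, one pretest) cannot support that. This follows from the design alone and needs no numerical assumption.

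The size does need one. With no training effect, 50 completers and a shared gain of 0.3 to 0.5 SD of change, the pooled time effect would be significant in about 55% to 93% of trials, against a nominal 5%. The document gives no test-retest figure, so the true gain could be smaller or larger. Hypothesis 2 is unaffected.

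One further inference should be avoided. A significant VR-versus-Nordic-walking contrast would show that the programmes differ, not that either improves on no training. A null contrast would not show that both work or that neither does.

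**What to change.** Restate hypothesis 1, the matching sentences in the Gait Adaptability Test section and the expectation in Differences in Effectiveness on Secondary Variables as descriptive change over time within each arm, and say that such change does not show that either programme works. State that the randomised contrast supports a conclusion only about a difference between the programmes. Add to Limitations of This Study that, without an untrained group or repeated baseline, gains common to both arms cannot be separated from repeat testing, expectation or other time effects.

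These are text changes only: no added arm, visit or analysis. The downside is a more modest claim under hypothesis 1.
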